### Exclusion criteria

Subject who does not meet any of the following will be excluded:1) Pregnant or lactating women2) Individuals with current or future fertility concerns3) Currently using Chinese patent medicine or traditional Chinese medicine decoction that bear similarities to the experimental drugs in terms of their constituent components4) History of chronic severe infection, any current infection and any malignant tumor5) Patients with severe primary diseases, such as those of the cardiovascular, cerebrovascular, hepatic, renal, and hematopoietic systems, and mental illness

### Sample size estimation

Based on previous study and physician experience (Xu et al., 2023), this study comprises two independent trials with comparative rates. Its objective is to explore whether there exists a disparity in the ACR20 response rate between the two groups after 12 weeks of treatment. The prior study conducted by our research group indicated that after 12 weeks of treatment, the ACR20 response rate was 87% for the YSTB combined with the MTX group, while it was 74% for the MTX group. Assuming *α* = 0.05 (two-tailed test) and achieving a power of (1-β) = 0.8, we utilized PASS 15 software to calculate sample sizes for the experimental and control groups, totaling 324 patients to be included.

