Yishen Tongbi decoction (YSTB) is an herbal formula consisting of six medicinal herbs, including *Tripterygium wilfordii* Hook.f [Celastraceae; *T. wilfordii radix et rhizoma*] (Kunming Shan Hai Tang) (THH), *Eucommia ulmoides* Oliv. [Eucommiaceae; *Eucommiae Cortex*] (Du Zhong), *Ligustrum lucidum* W.T.Aiton [Oleaceae; *Ligustri Lucidi Fructus*] (Nv Zhen Zi), *Eclipta prostrata* (L.) L. [Asteraceae; *Ecliptae Herba*] (Han Lian Cao), *Lycium barbarum* L. [Solanaceae; *Lycii Fructus*] (Gou Qi), and *Salvia miltiorrhiza* Bunge [Lamiaceae; *Salviae miltiorrhizae radix et rhizoma*] (Dan Shen). We analyzed the primary chemical constituents in the extracts and evaluated the quality of YSTB extracts using UPLC-Q-TOF-MS/MS (The chromatogram of YSTB is presented in Supplementary Material S1). It is protected by Patent No. ZL 2010110191532. X and has shown efficacy in treating RA over a decade of use. We have completed a 24-week double-blind, double-model, randomized controlled trial comparing the effectiveness and safety of YSTB with MTX for active RA. At week 4, the YSTB groups exhibited a significantly higher attainment of ACR20 and EULAR good or moderate responses, indicative of a more rapid therapeutic effect compared to MTX (Xu et al., 2023). In our animal experiments, we observed that YSTB possesses anti-inflammatory properties, inhibits synovial hyperplasia, and improves bone destruction (Hu et al., 2021; Jiao et al., 2023). Cell experiments revealed that YSTB could inhibit the activation and proliferation of ST486 cells (Burkitt’s lymphoma ST486 human B cells) and promote the apoptosis of ST486 cells (Hu et al., 2021). The Main components of YSTB is shown in Table 1.

**TABLE 1 T1:** Composition and action of Yishen Tongbi decoction.

Pinyin name	Full species name	Pharmacological effects	Toxicity	Doses (g)
Kunmingshanhaitang	*Tripterygium wilfordii* Hook.f. [Celastraceae; *Tripterygium wilfordii radix et rhizoma*]	Kunmingshanhaitang has strong anti-inflammatory and immunosuppressive effects, which can significantly improve joint swelling and pain and delay bone destruction in patients with RA Chatzidionysiou et al. (2017), Drosos et al. (2020), Yates et al. (2020), Fujii et al. (2024)	hepatotoxicity, nephrotoxicity, reproductive toxicity Ru et al. (2019)	25

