## Methods and analysis

### Study design

This study is a prospective, multicenter, real-world observational clinical trial conducted at two designated centers in China from October 2023 to August 2025. The study included a population of 324 patients with RA. Treatment schemes were determined by doctors based on individual patient conditions and preferences. One group will receive YSTB combined with csDMARDs, while the other group will receive bDMARDs/tsDMARDs combined with csDMARDs, or a combination of two csDMARDs. The study protocol has been approved by the Ethics Committee of the First Affiliated Hospital of Guangzhou University of Traditional Chinese Medicine (approval NO.K-2023-009) and registered with the Chinese Clinical Trial Registry (ChiCTR2300076073). The study flowchart is shown in Figure 1. The Standard Protocol Items: Recommendations for Interventional Trials (SPIRIT) figure is shown in Figure 2.

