### Interventions

This observational study is to evaluate the efficacy and safety of YSTB in the real-world hospital setting. Therefore, for the enrolled participants, there is no strictly defined treatment regimen. After evaluating the patient’s condition, the doctor chooses the most appropriate therapeutic medication treatment medication. Patients who receive YSTB (150 mL orally once a day) combined with csDMARDs to manage their condition will be divided into YSTB combined with csDMARDs group. Patients who are treated with bDMARDs/tsDMARDs, along with csDMARDs, or those using a combination of two csDMARDs, will be placed in the standard treatment group. As for specific drugs, common csDMARDs may include medications like Methotrexate, Leflunomide, or Apremilast, while tsDMARDs could consist of drugs such as Tofacitinib tablets or Baricitinib tablets. bDMARDs may include medications like Yisaipu. Nonsteroidal anti-inflammatory drugs (NSAIDs) or oral corticosteroids (prednisone ≤10 mg/days or the same dose) can be added when necessary. The medication information of the participants will be recorded in the case report form (CRF) at each follow-up.

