
Traditional Chinese medicine theory, clinical practice and many basic studies have shown that Yishen Tongbi decoction has a significant effect in the treatment of RA, but the therapeutic advantage of traditional Chinese medicine is still lack of high-quality evidence-based medicine. Therefore, the research group conducted a double-blind, randomized, controlled, non-inferiority trial of YSTB in the treatment of active RA, head-to-head comparison of the efficacy and adverse reactions of MTX (Xu et al., 2023). This clinical trial is the first RCT study in China to use traditional Chinese medicine compound prescription and MTX to conduct a head-to-head study in the field of RA treatment. This study uses CDAI as the main outcome index for a period of 24 weeks. The results showed that the standard rate of CDAI in YSTB group and MTX group were 67.4% (33/49) and 57.1% (28/49), respectively, and the risk difference was 0.102 (95% CI −0.089 to 0.293), indicating that Yishen Tongbi decoction was not inferior to MTX. In the secondary outcome index, compared with the MTX group, the YSTB group had a higher rate of good or moderate response to ACR20 (57.1% vs. 30.6%, *p* = 0.008) and good or moderate response to EULAR (61.2% vs. 34.7%, *p* = 0.009) at week 4, suggesting that YSTB took effect faster than MTX. The incidence of drug-related adverse events was 28.6% (14/49) and 22.4% (11/49) in the YSTB and MTX groups, respectively. There was no significant difference in the incidence of drug-related adverse reactions between the two groups (*p* = 0.487), and there was no serious non-reaction, which proved the safety of YSTB. Both YSTB and MTX groups showed impaired liver function (ALT >33 U/L) as the most frequent drug-related side effect, with rates of 14.3% (7/49) and 12.2% (6/49) respectively (*p* = 0.766). Although liver function abnormalities were more common than other adverse events, 4 patients in each group had slightly elevated levels (<2 times the upper limit), mostly asymptomatic, allowing trial completion. One YSTB patient with ALT of 123 U/L at week 12 normalized with outpatient liver protection. Gastrointestinal reactions occurred in 2.0% (1/49) in both groups (*p* = 1.000). Diarrhea led to study discontinuation in one patient per group, and one YSTB patient stopped due to paroxysmal palpitations. Leukopenia incidence was 2.0% in both groups, and one MTX patient appeared anemic. Menstrual irregularities affected 3.5% (3/86) of female patients (43 premenopausal) without significant group difference (*p* = 0.554) during the 24-week trial (Xu et al., 2023). This study provides high-quality evidence of evidence-based medicine for the treatment of RA with YSTB, and the relevant results are published in the first District Journal of the highest influencing factor in the field of traditional Chinese medicine.

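### The 87% vs 74% ACR20 planning rates do not match the prior trial as the article describes it or this study's control group, so the stated 80% power is unsupported for the comparison being made

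*Protocol article*

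**What the plan says.** The Sample size estimation section opens by referring to previous study and physician experience, with one citation, the group's 2023 randomised trial. It then credits its week-12 planning rates to the group's own earlier work and reports that "the ACR20 response rate was 87% for the YSTB combined with the MTX group, while it was 74% for the MTX group". With alpha "0.05 (two-tailed test) and achieving a power of (1-β) = 0.8", the authors used software to "calculate sample sizes for the experimental and control groups, totaling 324 patients to be included". It states no group sizes, allocation ratio or attrition rate.

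The cited trial is described in two other places:
- The Introduction calls it a "randomized controlled trial comparing the effectiveness and safety of YSTB with MTX for active RA".
- The Discussion calls it a head-to-head non-inferiority trial and reports two groups: "the standard rate of CDAI in YSTB group and MTX group were 67.4% (33/49) and 57.1% (28/49), respectively". The only ACR20 result given from it is at week 4 (57.1% vs 30.6%).

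For the present study, the Interventions section puts patients on YSTB plus csDMARDs in one group. Patients on a bDMARD or tsDMARD with csDMARDs, or "those using a combination of two csDMARDs, will be placed in the standard treatment group". Study design, the Figure 1 legend and the Discussion define control in the same way.

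**The concern.** The 13-point difference is the only stated basis for 324 patients and 80% power on the primary outcome. Two things do not fit.

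1. **Source.** The experimental rate is credited to YSTB combined with MTX, but the one study cited had no such arm as the article describes it. If 87% in fact belongs to YSTB alone, it is a rate for a different regimen from the one studied here.
2. **Comparator.** The 74% is an MTX rate. Under the operative definition, a patient on MTX alone is not in the control group, and the article gives no ACR20 rate for the regimens that are.

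Power for a difference in proportions depends heavily on the control rate. If that rate is not the one planned on, readers will credit the study with a power it may not have. The Discussion also hypothesises only that YSTB plus csDMARDs is not inferior to standard treatment, which sits uneasily with planning on a 13-point advantage.

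**Working it through.** **Inputs**
- Rates 0.87 and 0.74, two-sided alpha 0.05, power 0.80, total 324: Sample size estimation.
- Equal groups: assumed. The article gives no ratio, and "Treatment schemes were determined by doctors based on individual patient conditions and preferences".
- 10% attrition: assumed. No rate is stated.
- Control rates other than 74%: assumed. None is given for the actual control mix.

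**Step 1. Reproduce the plan's figure.** Pooled normal approximation, with p̄ = (0.87 + 0.74)/2 = 0.805:

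n per group = [1.960 × √(2p̄(1 − p̄)) + 0.8416 × √(p1(1 − p1) + p2(1 − p2))]² / (p1 − p2)²

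- First term: 1.960 × √(2 × 0.805 × 0.195) = 1.960 × √0.31395 = 1.0982
- Second term: 0.8416 × √(0.1131 + 0.1924) = 0.8416 × √0.3055 = 0.4652
- n = (1.5634 / 0.13)² = 144.6, so 145 per group and 290 in total
- With 10% attrition: 145 / 0.9 = 161.1, so 162 per group and 324 in total

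A continuity correction without attrition gives 160 per group, 320 in total, close to 324. The total therefore follows from the stated rates.

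**Step 2. Set the descriptions side by side.**

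| Item | Sample size estimation | Elsewhere in the article |
|---|---|---|
| Arms of the prior study | YSTB + MTX vs MTX | YSTB vs MTX, 49 per arm (Introduction, Discussion) |
| Week-12 ACR20 | 87% vs 74% | Not reported; only week 4, 57.1% vs 30.6% (Discussion) |
| Comparator | MTX | bDMARD/tsDMARD + csDMARD, or two csDMARDs (Study design, Figure 1, Interventions, Discussion) |

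**Step 3. Power if the control rate differs.** With m evaluable per group and control rate pc:

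power = Φ{[(0.87 − pc)√m − 1.960 × √(2p̄(1 − p̄))] / √(0.1131 + pc(1 − pc))}

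Example, m = 145 and pc = 0.78 (p̄ = 0.825): [0.09 × 12.042 − 1.960 × √0.28875] / √0.2847 = (1.0837 − 1.0532) / 0.5336 = 0.057, and Φ(0.057) = 0.52.

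| Assumed control rate | Power, 145 evaluable per group | Power, 162 evaluable per group |
|---|---|---|
| 70% | 94% | 96% |
| 74% (planned) | 80% | 84% |
| 78% | 52% | 57% |
| 80% | 36% | 40% |

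The 145 column is the consistent one if 324 already includes 10% attrition; the 162 column assumes no losses.

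**Step 4. Matching.** The Statistical analyses section matches on the propensity score with a calliper and without replacement, so some patients will be left unmatched. At the planned 87% vs 74%, and treating the matched groups as independent samples, 130 per group gives 76% power and 100 per group gives 64%. These group sizes are illustrations; the documents predict no matching yield.

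**The case against.** **The source may be another study.** The sentence giving the rates carries no citation of its own, the section also invokes physician experience, and the Objective and Discussion speak of earlier RCT studies in the plural. An unnamed source cannot be excluded. This stands as a limit on certainty. However, the article cites and describes only one such trial, and the comparator mismatch remains whatever the source.

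**The comparator is described more loosely elsewhere.** The Abstract lists csDMARDs as a standard-treatment subgroup without requiring two. The Objective asks whether YSTB adds benefit on top of csDMARDs. The Statistical analyses section matches to patients on conventional drugs alone. On those wordings an MTX rate is closer to the mark. This stands in part: it is a reason to reconcile the passages, because four places, including the one that assigns patients to groups, use the narrower definition.

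**The control rate could be lower than 74%.** Patients enter after at least 4 weeks of standard treatment and with disease that is still graded mild to severe, so a lower response is possible and power would then be higher. This stands, and is why the range runs both ways.

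**Stronger readings that the documents do not support:**
- A reader might infer that 324 is miscalculated. It is not; Step 1 reproduces it.
- A reader might note that no whole count out of 49 rounds to 87% or 74% and conclude that the rates are impossible. The Discussion says that 82 patients completed the trial, and completer denominators can give such rates (for example 34/39 = 87.2% and 32/43 = 74.4%). This shows nothing either way.
- A reader might conclude that a null result would be uninformative. Odds ratios with 95% confidence intervals are planned, and the Discussion's hypothesis is non-inferiority, so similar rates would still carry information.

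**Conclusion.** The point holds as a fault in the planning assumptions and should be fixed. As written, the 87% is attributed to an arm that the cited trial, by the article's own account, did not have, and the 74% belongs to a comparator outside the operative control definition. The stated 80% power is therefore not supported for YSTB plus csDMARDs against the control group enrolled.

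The size depends on a rate that the documents do not give. With 145 evaluable per group, a control rate four points above plan lowers power from 80% to 52%, and one four points below raises it to 94%. These figures assume equal groups, a true experimental rate of 87% (itself of uncertain origin) and no loss to matching, which would lower them further. No claim is made about which direction is true.

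**What to change.** Rewrite the sample size paragraph:
1. State which study, arms, analysis set and counts gave 87% and 74%, and correct the arm labels if they are wrong.
2. State and justify an assumed week-12 ACR20 rate for the control group actually enrolled. Bring the comparator wording in the Abstract, Objective and Statistical analyses into line with Study design and Interventions.
3. Keep 324. Replace the single 80% with power over a range of control rates on both sides of 74%, as in Step 3. Give equal groups, the 87% experimental rate and the attrition allowance as explicit assumptions, and note that unmatched patients reduce power.

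The cost is one paragraph plus small wording changes elsewhere. No extra patients and no change of analysis are needed. The price is that 80% would be shown as holding only under particular assumptions.

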### Interventions

This observational study is to evaluate the efficacy and safety of YSTB in the real-world hospital setting. Therefore, for the enrolled participants, there is no strictly defined treatment regimen. After evaluating the patient’s condition, the doctor chooses the most appropriate therapeutic medication treatment medication. Patients who receive YSTB (150 mL orally once a day) combined with csDMARDs to manage their condition will be divided into YSTB combined with csDMARDs group. Patients who are treated with bDMARDs/tsDMARDs, along with csDMARDs, or those using a combination of two csDMARDs, will be placed in the standard treatment group. As for specific drugs, common csDMARDs may include medications like Methotrexate, Leflunomide, or Apremilast, while tsDMARDs could consist of drugs such as Tofacitinib tablets or Baricitinib tablets. bDMARDs may include medications like Yisaipu. Nonsteroidal anti-inflammatory drugs (NSAIDs) or oral corticosteroids (prednisone ≤10 mg/days or the same dose) can be added when necessary. The medication information of the participants will be recorded in the case report form (CRF) at each follow-up.

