## Abstract

**Introduction:** Rheumatoid arthritis (RA) is a globally challenging and refractory autoimmune disease, constituting a serious menace to human health. RA is characterized by recurrent pain and is difficult to resolve, necessitating prolonged medication for control. Yishen Tongbi decoction is a traditional Chinese herbal compound prescribed for treating RA. We have completed a 3-year RCT study that confirmed the clinical efficacy of Yishen Tongbi decoction for RA. Notably, we observed a faster clinical remission rate compared to MTX by week 4 of treatment. In our forthcoming study, we intend to conduct a comprehensive assessment of the efficacy and safety of Yishen Tongbi decoction in the real-world treatment of RA through a prospective study.

**Methods and analysis:** This prospective, multicenter, real-world observational study will be conducted at two designated centers in China from October 2023 to August 2025. The study will include 324 patients with active rheumatoid arthritis. One group will receive Yishen Tongbi decoction combined with conventional synthetic disease-modifying antirheumatic drugs (csDMARDs). The other group will receive standard treatment. Standard treatment can be further divided into subgroups: csDMARDs, targeted synthetic disease-modifying antirheumatic drugs (tsDMARDs), and biologic disease-modifying antirheumatic drugs (bDMARDs). In each group, the number of tender joints, number of swollen joints, pain score, patient global assessment, physician global assessment, disease activity index (DAS28-ESR or DAS28-CRP), clinical disease activity index (cDAI), simplified disease activity index (sDAI) and relevant laboratory data will be compared. Clinical indicators and disease activity of the patients will be assessed at baseline, week 4 and week 12 after the initiation of treatment. The primary outcome will be the American College of Rheumatology 20% improvement criteria (ACR20) attainment rate among patients at week 12 after treatment. Every adverse event will be reported.

**Ethics and dissemination:** This study has been approved by the Ethics Committee of the first affiliated Hospital of Guangzhou University of traditional Chinese Medicine (NO.K-2023-009). The results of the study will be published in national and international peer-reviewed journals and at scientific conferences. The researchers will inform participants and other RA patients of the results through health education.

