### Objective

Based on previous RCT studies on YSTB, we will initiate a prospective real-world study to comprehensively assess the efficacy and safety of YSTB in RA treatment. Subgroup analyses will be used to evaluate the clinical remission effectiveness in RA patients receiving various treatment strategies. Furthermore, we will assess whether the combination of YSTB can provide additional significant beneficial results on the basis of csDMARDs.

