### Statistical analyses

Attempting to ensure equivalence in baseline characteristics of participants between the YSTB group and the conventional therapy group, a propensity score method will be performed. Variables involving age, sex, smoking history, BMI and other factors will be included into the logistic regression model to calculate a propensity score for each participant. Participants who used YSTB will be matched to those who receive conventional drugs alone based on the propensity score, using the greedy matching with a standard calliper width of 0.2 and without case replacement. Covariate balance of the matched cohort will be assessed using the mean standardized differences. When a |d| > 0.10, it is considered as an imbalance. Inverse probability of treatment weighting based on the propensity score will also be performed to evaluate the robustness of the matching results. Baseline demographic variables will be presented as means, medians, or percentages, and using Chi-square test, independent *t*-test, or Mann-Whitney *U* test, as appropriate. Outcomes of CDAI, SDAI, DAS-28, ACR20, ACR50, ACR70 will be analyzed by using Chi-square test and logistic regression. Odd ratios and 95% confidence intervals will be estimated. Subgroup analysis will be performed on age, gender, treatment regimens (CHM alone, conventional medication alone and the combination). All analysis will be tested with a two-sided alpha level of 0.05 except the logistic regression. For the missing data, the reasons why the data is missing will be analyzed, and multiple imputation will be used.

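### The compared groups are defined differently in the Abstract, Study design, Interventions and Statistical analyses, and some regimens, including a single csDMARD, fit no group under the Interventions rules

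*Protocol article*

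**What the plan says.** All quotes are from the protocol article.

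- **Interventions, freedom of treatment:** "for the enrolled participants, there is no strictly defined treatment regimen".
- **Interventions, YSTB group:** "Patients who receive YSTB (150 mL orally once a day) combined with csDMARDs to manage their condition". No limit is put on the number of csDMARDs, and nothing is said about a bDMARD/tsDMARD taken at the same time.
- **Interventions, standard group:** "Patients who are treated with bDMARDs/tsDMARDs, along with csDMARDs, or those using a combination of two csDMARDs". Study design and the Figure 1 caption give the same rule.
- **Abstract, standard group:** "Standard treatment can be further divided into subgroups: csDMARDs, targeted synthetic disease-modifying antirheumatic drugs (tsDMARDs), and biologic disease-modifying antirheumatic drugs (bDMARDs". Here csDMARDs stand as a subgroup with no two-drug condition.
- **Statistical analyses:** "Participants who used YSTB will be matched to those who receive conventional drugs alone". The subgroup list there splits treatment into CHM alone, conventional medication alone, and the two combined.
- **Objective:** the study will also assess "whether the combination of YSTB can provide additional significant beneficial results on the basis of csDMARDs".
- **Sample size estimation:** the ACR20 rate is taken as 87% for YSTB with MTX, "while it was 74% for the MTX group".

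The inclusion and exclusion criteria do not clearly close the gaps. They ask for at least four weeks of standard RA treatment and bar Chinese medicines similar to the study drug. They do not mention YSTB with a bDMARD/tsDMARD, or single-drug treatment.

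**The concern.** In a non-randomised study, the group definition is the exposure definition. Here it changes from section to section, and the sections disagree on patients who are likely to occur: the Introduction itself calls csDMARDs first-line and MTX the current standard. If the rules are not reconciled, group membership may be settled while the data are being analysed, when outcomes can be seen.

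The disagreement also reaches the study's own aims. The sample size and the add-on objective both rest on YSTB added to a csDMARD background. The standard group of the Interventions section is a different comparator: it contains bDMARD/tsDMARD users and leaves out patients on one csDMARD.

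**Working it through.** **1. The written rules applied to each regimen.** In the Statistical analyses column I read conventional drugs as any antirheumatic drug other than YSTB.

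| Regimen | Study design and Interventions | Abstract | Statistical analyses |
|---|---|---|---|
| YSTB + one csDMARD | YSTB | YSTB | exposed |
| YSTB + two csDMARDs | YSTB; also meets the standard rule as written | YSTB | exposed |
| YSTB + csDMARD + bDMARD/tsDMARD | meets both rules as written | not addressed | exposed |
| YSTB alone | neither | neither | exposed; CHM-alone subgroup |
| One csDMARD | neither | standard | control |
| Two csDMARDs | standard | standard | control |
| bDMARD/tsDMARD + csDMARD | standard | standard | control |
| bDMARD/tsDMARD alone | neither | standard | control |

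Three of the eight regimens fit no group under Interventions: one csDMARD, bDMARD/tsDMARD alone, and YSTB alone. Two meet both rules on a literal reading. If conventional is meant as conventional synthetic only, the bDMARD/tsDMARD rows leave the control column and the sections differ further. The single-csDMARD patient is a control on either reading.

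**2. The plan's own figure.** Inputs from Sample size estimation: 87% and 74%, two-sided alpha 0.05, power 0.80. Equal arms are assumed, as no ratio is given. With the pooled-variance formula:

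n = [1.960 × √(2 × 0.805 × 0.195) + 0.842 × √(0.87 × 0.13 + 0.74 × 0.26)]² / 0.13²

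= (1.098 + 0.465)² / 0.0169 ≈ 144.6, so 145 per arm and 290 in total.

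Allowing 10% dropout (not stated in the article), 145 / 0.9 = 161.1, so 162 per arm and 324 in total, the stated number. The continuity-corrected formula gives 160 per arm, or 320. The arithmetic is therefore sound for 87% versus 74%. What does not match is the control regimen: the 74% belongs to an MTX group, and one csDMARD has no place in the standard group of Interventions.

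**3. What losing patients would cost.** The article does not say how many patients fit no group, so the shares below are assumptions. Taking the planned rates as true and arms as equal, power is 84.3% at 162 per arm.

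| Share lost from the comparison | Patients left | Power |
|---|---|---|
| 5% | 308 | 82% |
| 10% | 292 | 80% |
| 20% | 259 | 75% |
| 30% | 227 | 70% |

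The margin over 290 is 324 − 290 = 34 patients, about 10%, with nothing then left for dropout or unmatched patients.

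**The case against.** **The groups are clear to a normal reader.** The article keeps one contrast throughout: YSTB with csDMARDs on one side, standard treatment on the other. No section plans YSTB with a biologic. The Statistical analyses section opens by naming a YSTB group and a conventional therapy group, so its later reference to participants who used YSTB may be shorthand for the Interventions group. It also limits controls to conventional drugs alone, which settles YSTB with two csDMARDs as exposed. Much of this stands, and the overlap is the weaker half of the point. What remains is that no section excludes or places YSTB with a csDMARD and a bDMARD/tsDMARD, and that shorthand does not explain a CHM-alone subgroup.

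**Eligibility may remove the single-csDMARD patient.** If the required four weeks of standard RA treatment means the Figure 1 definition, such a patient could not enter. But the Introduction calls MTX the standard treatment, and the Abstract counts csDMARDs as a standard subgroup, so that reading is not secured.

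**An article leaves exposure coding to fuller documents.** That would answer a complaint about missing detail. Here, sections of the same article give different rules.

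**Stronger readings that the documents do not support.** A reader might infer that single-csDMARD patients offer the only contrast that isolates what YSTB adds. They do not: YSTB with two csDMARDs against two csDMARDs isolates an add-on effect too. Nor are these patients plainly removed from the study, since two sections exclude them and two appear to include them. A reader might also want to put a number on the bias from biologic users counted in the YSTB group. The documents give neither their share nor their extra response. The standard group contains such users as well, so the net bias could run against YSTB. The planned 13-point difference belongs to another contrast and is no yardstick for it.

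**Conclusion.** The point holds as an inconsistency of definition that should be corrected. The firm elements are the single-csDMARD patient (no group under Study design and Interventions, standard in the Abstract, control in Statistical analyses), the CHM-alone subgroup that Interventions cannot contain, and the unplaced patient on YSTB, a csDMARD and a bDMARD/tsDMARD. The sample size and the add-on objective rest on a csDMARD-background contrast that the Interventions standard group does not match.

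No size can be given for the effect on the ACR20 comparison, because regimen shares are not reported. The power figures illustrate only the loss of numbers, and they assume the planned rates, equal arms and the listed shares. The inconsistency does not show that the total of 324 was miscalculated, or that the result would favour YSTB.

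**What to change.** Reconcile the Abstract, Study design, Interventions and Statistical analyses so that all four use one set of mutually exclusive and exhaustive analysis groups, before outcomes are compared.

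1. Assign each patient from the treatment in use at the start of follow-up. The case report form already records medication.
2. State for every regimen which group it joins. Give a rule for regimens that fit neither or both, for example descriptive reporting outside the primary comparison. This must cover YSTB with a csDMARD and a bDMARD/tsDMARD, and YSTB alone.
3. Say whether a single csDMARD and a bDMARD/tsDMARD alone count as standard treatment, and align the subgroup list with that answer.
4. For the add-on objective, prespecify a comparison of YSTB plus csDMARDs with csDMARDs without YSTB or a bDMARD/tsDMARD, including single-csDMARD patients.
5. State which comparison the 87% and 74% refer to.

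This concerns analysis groups only. Which regimens belong in each group is for the investigators to settle, and treatment choice stays with the doctors. The cost is protocol wording. The downside is that some patients leave the primary comparison. Their share is not given in the documents, so it should be counted from baseline medication records before the groups are fixed.
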